### Study population

Study participants are paediatric (1–15 years) and adult (≥16 years) burns patients presenting within 24 hours of injury to participating burns centres that include but are not limited to: (1) West Midlands Regional Burns Centre, Queen Elizabeth Hospital Birmingham (QEHB), Birmingham, UK; (2) Paediatric Burns Centre, Birmingham Children’s Hospital (BCH), Birmingham; (3) St Andrew’s Centre for Plastic Surgery and Burns, Broomfield Hospital, Chelmsford, Essex, UK.

Screening of the enrolment log generated for patients recruited into our previous observational study,^18^ revealed a predominantly male (61%) and Caucasian (79%) patient cohort. Given that the West Midlands Regional Burns Centre will again serve as the primary site of patient recruitment, we anticipate a similar patient demographic for the SIFTI-2 study.

Patients will be identified by research clinicians or the admitting doctor from the burns research team and screened for study eligibility using the following inclusion and exclusion criteria:

#### Inclusion

Patients aged 1–15 years admitted with a ≥20% TBSA burn.Patients aged 16 years and over admitted with a≥15% TBSA burn.

#### Exclusion

Associated multiple injuries with an injury severity score (ISS) >25.Decision not to treat due to the severity of the injury. This decision will be made at the time of hospital admission.Patients with chemical or deep electrical burns.Patients receiving glucocorticoid treatment.Patients with active malignancy.Patients with multiple limb amputations (amputations would skew the calculation of TBSA scores).Patients with known long-term infections (eg, hepatitis B and C, HIV).

Alongside burns patients, a maximum of 100 adults and 10 children will be recruited to serve as a cohort of age-matched healthy controls (HCs), with the only exclusion criterion being current treatment with anti-coagulant medication or an acute infection.

Adult HCs can be recruited from age 16 years, with no upper age limit. Enrolment of up to 100 healthy adults will enable us to undertake diverse sampling of the adult population, allowing us to control for as many of the variations that encompass this broad age range as possible (eg, general physical condition, concurrent medical conditions and drug therapies, past exposure to disease or injury and different degrees of physiological ageing). Adult HC volunteers will be recruited through advertisements disseminated at the QEHB, BCH, the University of Birmingham campus and via online newsletters. When an expression of interest for study participation is received by the burns research team, a patient information leaflet (PIL) detailing the conditions of the study will be sent to the volunteer. All subjects who receive a PIL will be recorded on a screening log that will be held in the site file at the QEHB. Adult volunteers will attend the QEHB to participate in the study.

The paediatric HC group will consist of children undergoing elective plastic surgery procedures at the BCH. These surgeries will include mole removal, correction of prominent ears, revision of plastic surgery and cosmetic type surgery. In terms of age range and a lack of other health conditions or ongoing medical treatments, paediatric HCs will represent a more homogeneous cohort when compared with our adult HC group. Thus, we expect to observe much less variability in the baseline immune profiles of paediatric HCs. This factor, combined with the complexity of recruiting paediatric HCs, is the reasoning behind our decision to enrol a maximum of 10 healthy paediatric volunteers into the SIFTI-2 study.

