For adult HCs, the following clinical information will be recorded: date of birth, gender, weight in kilograms, height in metres and smoking status (active, ex-smoker or never smoked). The same details in addition to information relating to past medical history/congenital anomaly history will be recorded for paediatric HCs.

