### Data analysis

Data will be assessed for normality using the Shapiro-Wilk test. Normally distributed data will be presented as mean values with SD. Non-normally distributed data will be presented as median values with IQR. Comparisons of baseline continuous data (eg, demographics, injury characteristics) between two groups (eg, HCs vs burns patients or septic vs non-septic patients) will be conducted using an unpaired Student’s t-test for normally distributed data or the Mann-Whitney U test for non-normally distributed data. Categorical baseline data will be compared using a χ^2^ test. Laboratory data obtained from HCs and patients across the different sampling time points will be compared using either a one-way analysis of variance with a Dunnett post hoc test for normally distributed data or a Kruskal-Wallis test with a Dunns post hoc test for non-normally distributed data. A p <0.05 will be considered statistically significant.

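### Adult controls are called age-matched, but nothing described ties their age to the patients' and the control-versus-patient laboratory comparison is unadjusted, so age or sex differences could be read as burn effects

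*Protocol article*

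**What the plan says.** The control group is described under Exclusion in the protocol article: "a maximum of 100 adults and 10 children will be recruited to serve as a cohort of age-matched healthy controls (HCs". The same section sets out how adult controls enter the study.

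- Age: "Adult HCs can be recruited from age 16 years, with no upper age limit".
- Source: "Adult HC volunteers will be recruited through advertisements disseminated at the QEHB, BCH, the University of Birmingham campus and via online newsletters".
- Eligibility: "with the only exclusion criterion being current treatment with anti-coagulant medication or an acute infection".
- Purpose of enrolling up to 100: diverse sampling of adults, "allowing us to control for as many of the variations that encompass this broad age range as possible". Physiological ageing is among the variations listed.

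Paediatric controls are described separately, as children having elective plastic surgery at the children's hospital.

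For the patients, Study population reports that the previous study's log "revealed a predominantly male (61%) and Caucasian (79%) patient cohort" and expects a similar mix. Table 1 records patients' age and sex. For adult controls, the text after Table 1 lists "date of birth, gender, weight in kilograms, height in metres and smoking status".

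On analysis, the Data analysis section states: "Laboratory data obtained from HCs and patients across the different sampling time points will be compared using either a one-way analysis of variance" with Dunnett comparisons, or Kruskal-Wallis with Dunn's comparisons if the data are not normal. No covariate is named.

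Data collection and patient outcomes gives the use of this comparison: to establish, in adults and children, how long immune changes attributed to the burn last relative to healthy controls.

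**The concern.** Age-matched is a claim about design. It tells the reader that a control-versus-patient difference is not an age difference. Matching to the ages of burns patients and sampling the adult population diversely are different aims, and the recruitment text describes only the second. Diverse sampling does not control for anything unless the analysis uses the recorded variables, and the named tests do not.

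At stake is the inference about duration. Patients are sampled to month 24 and judged against these controls. Soon after injury the burn effect may be large enough to swamp a modest difference in age or sex mix. At months 3 to 24 it may not be. A difference caused by who volunteered could then look like persistent immune change, or could hide recovery.

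**Working it through.** **1. The plan's own figure.** Sample size gives 220 patients and 10% drop-out: 220 / (1 − 0.10) = 244.4, rounded up to 245. This reproduces. With 60% sepsis there are 132 septic and 88 non-septic patients. The exact lower 95% limits are 0.836 for a sensitivity of 0.90 and 0.593 for a specificity of 0.70, in line with the stated 84% and 59%. None of this involves the controls. No calculation is given for the 100 adult and 10 child controls.

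**2. Label against procedure (adults).**

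| Element | What the article states | Ties control age to patient age? |
|---|---|---|
| Label | Age-matched | Claims to |
| Age rule | 16 and over, no ceiling | Only through the adult/child cut-off |
| Source | Adverts and newsletters | No |
| Exclusions | Anticoagulants, acute infection | No |
| Aim | Diverse sampling | No |
| Laboratory test | One-way ANOVA/Dunnett or Kruskal-Wallis/Dunn | No covariate |

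The mixed models described later in Data analysis follow a paragraph about septic versus non-septic patients. They are not offered for the control comparison.

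**3. Illustration of size.** Every effect below is an assumption, because the article supplies none. Take 100 adult controls, 200 adult patients (the adult share of the 245 is not stated), no burn effect, and a single two-sided comparison at 0.05. If a marker drifts by b SD per decade and the mean ages differ by g years:

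- spurious difference d = b × g / 10
- standard error = √(1/100 + 1/200) = 0.1225 SD
- false-positive rate = Φ(d/0.1225 − 1.96) + Φ(−d/0.1225 − 1.96)

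Worked case, b = 0.1 and g = 10: d = 0.10, d/0.1225 = 0.816, rate = Φ(−1.144) + Φ(−2.776) = 0.126 + 0.003 = 0.129.

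| Drift per decade | Gap 5 years | Gap 10 years | Gap 15 years |
|---|---|---|---|
| 0.05 SD | 5.5% | 7% | 9% |
| 0.1 SD | 7% | 13% | 23% |
| 0.2 SD | 13% | 37% | 69% |

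With 150 patients the middle row is 7%, 12% and 21%, so the assumed number of patients matters little.

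For sex, d = (0.61 − control proportion male) × sex effect. With controls 50% male and an effect of 0.2 SD, d = 0.022 and the rate is 5%. With controls 30% male and an effect of 0.5 SD, d = 0.155 and the rate is 24%.

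The plan's Dunnett procedure would use a stricter critical value than this single comparison, so these are not the plan's actual error rates. They show how the bias scales. The correction for multiple comparisons does not remove the bias, because the same control group is the reference at every time point.

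**The case against.** The case on the other side is substantial, and much of it stands.

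- **First-come entry.** A reader might infer that any adult who answers an advert is enrolled until 100 are reached. The article does not say so. It gives an eligibility range, a maximum and a screening log from which selection could be made. A floor of 16 with no ceiling is also the adult patients' own range, so a matchable pool would need it.
- **Detail held elsewhere.** A matching procedure could sit in the full protocol, and covariates in an analysis plan. That is fair for the mechanics of matching. It does not cover the rest, because the article states a recruitment aim that differs from matching and names the unadjusted tests itself.
- **Children against a mostly adult reference.** Since 100 of 110 possible controls (91%) are adults, a reader might infer that children are compared with a largely adult group. The documents do not support this. The Exclusion section describes separate adult and paediatric control groups and justifies the 10 children by that group's own homogeneity. Nothing says the groups are pooled. The article merely does not state the separation in its analysis.
- **Sex.** A reader might take the 61% male figure as a target that the controls miss. Only age matching is claimed. The figure describes expected patients, so sex is a source of confounding to adjust for and not a broken promise.
- **Baseline tests.** The sentence that contrasts controls with burns patients by t-test or Mann-Whitney concerns baseline data. Applied to age, it would reveal an imbalance. It is not the defect; the sentence on laboratory data is.

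**Conclusion.** The point holds in a limited form. For adults, the age-matched label is not supported by the recruitment described, and the named laboratory comparison does not adjust for age or sex. The inference about how long immune change lasts is therefore exposed to differences between volunteers and patients, chiefly at months 3 to 24.

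The size of the bias is unknown. The illustrative false-positive rates run from near nominal (5.5%) to 69% and depend wholly on the assumed drift and age gap. If the adult groups turn out similar in age and sex, there is little bias. The primary objective concerns sepsis among burns patients and does not rest on a control comparison, so neither it nor the 245 changes.

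**What to change.** In Data analysis, replace the unadjusted adult control-versus-patient laboratory comparison with a regression model adjusted for age and sex, on a transformed scale where a marker is skewed. Comparisons of each time point with controls can be kept within that model. State that adults are compared with adult controls and children with paediatric controls. Report the age and sex distributions of adult controls beside those of adult patients, since adjustment extrapolates where the ages do not overlap.

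In the control paragraph under Exclusion, either frequency-match adult controls to patients by age band or drop the age-matched label. Sex quotas are not needed, because adjustment deals with sex.

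The cost is small: two covariates already recorded for patients and controls, no new data and no change in sample size. Matching would mean tracking age bands on the existing screening log and declining some volunteers. The article puts the study's estimated end at December 2025. If control recruitment has already closed, the adjustment and the wording change remain available.

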### Data collection and patient outcomes

In this prospective longitudinal study, data will be acquired from burns patients at the following 19 postinjury time points: days 1–14, day 28 (±3 days) and months 3, 6, 12 and 24 (±2 weeks). Patient enrolment into the study began on 27 November 2016, with an estimated end date of December 2025.

Across the settings of paediatric and adult burns, a significant number of studies have undertaken serial blood sampling to investigate the short (<1–7 days), medium (8–34 days) and long (35–1100 days)-term inflammatory response to thermal injury and its relationship with patient outcome.^22–28^ In contrast, very little data currently exist on the acute and long-term effects of thermal injury on the immune system.^19 24 29^ Thus, generating data on the kinetics of the immune response to burn injury via serial sampling in both our adult and paediatric cohorts will allow us to not only establish how long burn-induced changes in immunity persist for, when compared with HCs, but also compare the immune response of septic and non-septic burns patients over time. Generating and interrogating such novel data may provide mechanistic insights into the long-term health complications reported by survivors of burn trauma, which include an increased susceptibility to respiratory infections.^30^

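### A person with an earlier burn can enter as a healthy control, so the reference for how long burn effects last may include the exposure under study

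*Protocol article*

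**What the plan says.** All of this is in the protocol article.

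- **Control eligibility (Exclusion).** Up to 100 adults and 10 children serve as age-matched healthy controls, "with the only exclusion criterion being current treatment with anti-coagulant medication or an acute infection".
- **Adult controls (Exclusion).** The larger adult number is meant to cover the varied background of adults, including "past exposure to disease or injury and different degrees of physiological ageing". Recruitment is by advertisement, including at both Birmingham hospitals with a participating burns centre.
- **Child controls (Exclusion).** "The paediatric HC group will consist of children undergoing elective plastic surgery procedures at the BCH". The procedures are listed: "These surgeries will include mole removal, correction of prominent ears, revision of plastic surgery and cosmetic type surgery". The children are expected to have "a lack of other health conditions or ongoing medical treatments, paediatric HCs will represent a more homogeneous cohort", which is part of the reason for capping them at 10.
- **The hospital (Study population).** The participating centres include "Paediatric Burns Centre, Birmingham Children’s Hospital (BCH), Birmingham".
- **Use of the controls (Data collection and patient outcomes; Data analysis).** Serial sampling up to month 24 is to "establish how long burn-induced changes in immunity persist for, when compared with HCs". Laboratory data from controls and patients are compared across the sampling times.
- **Data recorded on controls (Demographic and physiological data).** For adults: date of birth, gender, weight, height and smoking. For children: the same, plus past medical and congenital anomaly history.

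**The concern.** In a persistence comparison the controls stand for people without the exposure. Variation in their age, illnesses or medicines adds noise and may be wanted, as the article argues for adults. An earlier burn is different, because it is the exposure whose lasting effect is being measured.

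If burn effects fade completely, admitting such people does no harm. If they last, previously burned controls carry part of the effect, and the patients appear to have returned to normal sooner or more fully than they have. The error therefore arises only when there is a lasting effect to find, and it works against finding it.

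Children are the more exposed group, because at most 10 controls form their whole reference.

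**Working it through.** **Is a previously burned person eligible?** The article does not simply leave the matter unmentioned. It describes anticoagulant treatment or acute infection as the only exclusion, so the list is closed. For adults, past injury is named among the variations to be sampled. For children, revision surgery is listed with no limit on why the first operation was done. The expected lack of other health conditions is a description and not a criterion, and a healed burn need not count as a current condition. On the text, such a person is eligible.

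**What would it do to the comparison?** The plan gives no figure for this point, so the size can only be illustrated.

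- From the article: n = 10 child controls and n = 100 adult controls, both maxima.
- Assumed: k controls have an earlier burn, and each carries a fraction c of the patients' late effect Δ.

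The control mean moves from μ to μ + c(k/n)Δ. The patient-versus-control difference becomes Δ(1 − ck/n), so the proportional loss is ck/n.

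| Group | k | c | Loss = ck/n |
|---|---|---|---|
| Children, n = 10 | 1 | 1 | 1/10 = 10% |
| Children, n = 10 | 1 | 0.5 | 0.5/10 = 5% |
| Children, n = 10 | 3 | 1 | 3/10 = 30% |
| Adults, n = 100 | 1 | 1 | 1/100 = 1% |
| Adults, n = 100 | 5 | 1 | 5/100 = 5% |

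The formula holds for means. Data analysis uses the Kruskal-Wallis test with Dunn's post hoc test for non-normal data, where the direction is the same but ck/n does not apply directly.

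**How likely is at least one such child among 10?** If a share f of the source population has an earlier burn, the chance is 1 − (1 − f)^10:

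- f = 5%: 1 − 0.95^10 = 40%
- f = 10%: 1 − 0.90^10 = 65%
- f = 20%: 1 − 0.80^10 = 89%

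The article gives no value for f.

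**Does it touch the sample size?** No. The stated total follows from 220/(1 − 0.10) = 244.4, rounded up to 245. It rests on sensitivity and specificity among burns patients and involves no control comparison.

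**The case against.** The case on the other side has real weight.

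- **The procedure list does not mention burns.** A reader might infer that revision surgery at this hospital means burn-scar revision, and that burned children will be enrolled. The documents do not support that. The link rests only on the hospital also housing a burns centre. What stands is that such a child is not excluded.
- **Breadth in adults is deliberate.** The article argues for diverse sampling, and with up to 100 adults a few affected people change little. This stands. Diversity still does not require people with the exposure under study.
- **The full-effect assumption is a ceiling.** Study patients have burns of at least 20% of body surface (children) or 15% (adults). An earlier burn in a control could be of any size and age, so c may be well below 1. A reader might take 10% to 30% as the expected bias in children, but neither k nor c is known. Those figures are illustrations only.
- **Chance error is larger.** With 10 controls the standard error of the control mean is SD/√10 = 0.32 SD. For an assumed late difference of 0.5 to 0.8 SD, one fully affected child shifts the result by 0.05 to 0.08 SD, and three by 0.15 to 0.24 SD. All are below one standard error. This stands as a reason to rank the point low. The shift is nevertheless in one direction and cheap to prevent.
- **The children's history is recorded.** An earlier burn could therefore be found at analysis. This stands and is used in the fix, but the article does not say that the history will be used in this way.

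**Conclusion.** The point holds as a minor weakness in control eligibility. A person with an earlier burn can be a healthy control, including a child whose revision surgery followed a burn, if there is such a child. If burn effects last, the patient-versus-control comparisons up to month 24 would then understate persistence.

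The bias cannot be sized from the article. The only firm bound is conditional: in a full group of 10, one child carrying no more than the patients' effect lowers a mean difference by at most 10%. In a group smaller than the cap, one child would be a larger share.

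Two wider conclusions are not supported. First, the article plans no sampling after month 24 (±2 weeks), so nothing follows about effects beyond that time. Second, the primary objective is not affected: it relates day 1 biomarkers to later sepsis among burns patients and contains no patient-versus-control comparison.

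**What to change.** 1. Add to the control exclusions: *any previous burn injury that needed hospital care, or surgery for a burn scar*. Ask one matching screening question of every adult volunteer and of every child or parent.
2. For child controls already enrolled, use the recorded past medical history to leave such children out of the control comparisons, or do so as a sensitivity analysis.
3. For adult controls already enrolled, the listed data hold no medical history, so an earlier burn cannot be identified from them. State this as a limitation of the persistence comparison.

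**Cost.** One line of eligibility text and one question. A few volunteers may be lost, which matters most in a child group capped at 10. Patient enrolment began in November 2016 with an estimated end of December 2025, so the new exclusion may reach few controls. For controls already in the study, steps 2 and 3 do the work.

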### Consent

Patients who meet study inclusion criteria and are deemed suitable for enrolment into the SIFTI-2 study will be assessed for capacity and assigned to one of the following three groups for the appropriate informed consent process: (1) adult patients with mental capacity, (2) adult patients lacking mental capacity or (3) children (aged<16 years). Details on the informed consent procedure for each of these groups are outlined below and summarised in figure 1.

**Figure 1 F1:**
[figure not shown]
Flow chart of patient screening and the consent procedure. MCA, Mental Capacity Act; TBSA, total body surface area.

#### Adult patients with mental capacity

Patients will be provided with a PIL that outlines the research study. If, after a discussion with the burns research team, the patient agrees to participate, they will be provided with and asked to sign a study consent form.

